#### Plans to give access to the full protocol, participant level data and statistical code {31c}

The full protocol, non-identifiable participant level data and statistical code may be available for sharing once the trial has ended. All requests will be approved by the Chief Investigator (CI), [name] ([contact]).

### Oversight and monitoring

#### Composition of the co-ordinating centre and trial steering committee {5d}

The trial will be overseen by the Trial Management Group (TMG) and a Trial Steering Committee (TSC). The TMG will be responsible for the day-to-day management of the trial. It includes individuals at the University of Birmingham (Chief Investigator, Trial Manager, Trial Co-ordinator, Clinical Trials Unit management staff) and Anandaban Hospital, The Leprosy Mission Nepal (Principal Investigator, local Project Manager and patient representatives). The TMG will meet monthly by teleconference. The Trial Steering Committee provides overall supervision of the trial and will ensure that it is conducted in accordance with the principles of Good Clinical Practice and other relevant regulations. Meetings will be scheduled before enrolment and after each meeting of the Independent Data Monitoring Committee and more frequently during the analysis phase. The TSC includes an independent chair and members with clinical expertise.

#### Composition of the Data Monitoring Committee, its role and reporting structure {21a}

The Data Monitoring Committee will review safety and efficacy data during the active phase of the trial. They will advise on the continued recruitment of trial participants. They will meet either by teleconference or face-to-face. This committee consists of an independent chair, a statistician and members with clinical and methodological expertise.

#### Adverse event reporting and harms {22}

The Principal Investigator in Nepal, [name], is responsible for recording all adverse events (AEs) and reporting any serious adverse events (SAEs) to the Chief Investigator and University of Birmingham Clinical Trials Unit (BCTU) within 24 h of becoming aware of such an event. A SAE form will be available on the data collection tablets and a database of any events will be maintained. The Trial Management Group, Chief Investigator and the BCTU will review any SAE forms. The Trial Steering Committee will periodically review all safety data and liaise with the Independent Data Monitoring Committee regarding any safety issues. Any deaths will be reported to the Sponsor irrespective of whether the death is related to the disease progression, the intervention or an unrelated event.

#### Frequency and plans for auditing trial conduct {23}

The trial is audited and monitored by the Sponsor, the University of Birmingham.

#### Plans for communicating important protocol amendments to relevant parties (e.g. trial participants, ethical committees) {25}

Any protocol amendment will be reported to the Trial Management Committee for approval. The Sponsor, University of Birmingham Biomedical and Scientific Research Ethics Committee and the Nepal Health and Research Council will subsequently be notified.

#### Dissemination plans {31a}

We will publish and disseminate through the usual academic channels, including peer reviewed journals and at academic conferences. Our dissemination plans include close liaison with The Leprosy Mission to engage affected people and communities and to ensure that the results are disseminated widely. Other dissemination plans include bite-sized research reports in lay format, public announcements in communities in LMICs, policy briefings, print and online media, the Chief Investigator’s News Blog (680+ subscribers), institutional and professional social media accounts and websites.

## Discussion

This protocol describes an individually randomised control trial to evaluate a treatment using autologous blood products L-PRF, to promote ulcer healing in leprosy. Despite the promising anecdotal evidence regarding this treatment, high-quality, empirical data are currently unavailable [12, 14].

Most of the evidence on ulcer healing, including the Cochrane review [12], is based on proportion of ulcers healed (completely epithelialized) by 42 days. This is sub-optimal because complete epithelialisation is a clinical decision that is also used to decide on discharge. This provides an opportunity for observer (outcome) bias. For this reason, we will measure rate of healing. These measures are all made centrally (in Birmingham) by two observers who are ‘blind’ to intervention status.

Activity measurements are not a primary outcome measure in our study. However, by collecting step-count daily and over the course of the inpatient stay over the periods specified above, we can exclude activity as a confounding factor in any differences found in ulcer healing rates between intervention and control groups.

We are also planning to do a range of nested studies. Given sufficient time and resources, we hope to video tape a subset of dressing changes (five intervention and two controls selected at random in Birmingham) as a means of photograph supervision and for additional quality control. We will also develop a more detailed health economics protocol. Finally, we will develop follow on studies based on the results of the trial.

We are using three methods to measure the rate of ulcer healing and time to complete re-epithelialisation. Readers might wonder at such an extensive set of methods and consider this ‘overkill’. Our rationale for using these multiple ulcer measurement methods is two-fold. First, it is crucially important in our judgement to create a situation where results cannot be explained away by measurement error (for all that measurement error is more of a threat to precision than to accuracy). Second, we wish to contribute to the methodological literature on ulcer measurement. As investigators we hope that the results will be consistently null or positive (or even negative). However, we realise that we may end up with results that toggle around the conventional statistical threshold , say, according to ulcer measurement method or whether or not adjustment had been carried out for any discrepancy in ulcer size at base-line. In that case, we will simply report the different results and allow the reader to make an interpretation. We will not (miss) use statistical tests as decision rules.

By using a randomised control method, alongside standardised blindly assessed photographs, and information on activity, this research will provide robust evidence on the clinical and cost-effectiveness of L-PRF in the treatment of leprosy ulcers. Data collection and ulcer assessment follows a ‘closed-loop’ such that the photograph and image can follow only one pathway from camera to completed measurement. An additional benefit is the evaluation of the effects of treatment on quality of life for people living with the effects of leprosy. The findings will also be relevant to other ulcerative conditions, particularly diabetes, where ulcers similarly result from peripheral nerve damage. The results will improve our understanding of the scalability of this treatment across low-income countries for ulcer healing in leprosy and other similar conditions.

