#### Activity measurement

All participants will be invited to wear a pedometer (Model: Mi Smart Band 5, Model: XMSH10HM) on the ankle of their non-affected limb (or non-index case affected limb) which they will wear from the first dressing change until 42 days (the point where cross-over may occur) or discharge, whichever comes first. This will act as a proxy measure of weight bearing and enable us to monitor activity across intervention and control groups and thereby evaluate whether the level of activity is similar across groups.

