#### Outcomes {12}

The main end-points will be:
‘Rate of healing’ based on two observations per week of ulcer size censored at 42 days (cm^2^ per unit time). We will estimate the effect of the intervention on the change in the ulcer size per unit time, i.e. the rate of healing (see Statistical Analysis).Time to complete re-epithelialization (right-censored at 42 days).

Both end-points will be analysed with and without adjustment for baseline characteristics (trial ulcer area and participants’ age), but we prefer unadjusted outcomes in randomised studies and therefore declare them as ‘primary’.

Secondary end-points:
Rate of healing based on two observations per week up to 70 days (cm^2^ per unit time) (calculated as described below).Time to complete re-epithelisation (observed up to 70 days).Generic quality of life (QoL) measured at first dressing change, fortnightly during in-patient stay and at 6-month follow-up, using the EQ-5D 3L. This scale has previously been used and validated in a Nepali population [17]. As far as we are aware, there is no valuation tariff in the Nepalese population, although this may change by the time that the analysis starts. Therefore, we propose not to prespecify the tariff but instead select the tariff at a later date. We note that tariffs are currently available for nearby countries including Sri Lanka [18] and China [19, 20].Longer-term outcomes measured at 6-month follow-up from randomisation will be proportion with:
i.Recurrence of treated ulcer;ii.Appearance of new ulcer;iii.Anatomical changes in the limb;Days hospitalised prior to discharge and total (to include any readmission due to leprosy/ulcers) by 6 months.Health economic information:
i.Number of visits to any healthcare facility from discharge to the end of follow-up at 6 months.ii.Data on the time taken to change dressings at the twice weekly changes.

Rate of healing will be assessed from blindly assessed photographs (Fig. 2). However, as complete healing may trigger discharge, we will monitor for cases discharged before the blinded assessor in Birmingham has noted complete re-epithelization.

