### Data collection and management

#### Plans for assessment and collection of outcomes {18a}

Demographic data (age and sex), clinical data (number and size of ulcers), concurrent diseases will be collected for all consenting participants before randomisation (Fig. 1). Data on quality of life (QoL) will be collected fortnightly from first dressing change until discharge. Ulcers will be assessed twice weekly (see below) during the participant’s hospital stay, to a maximum of 70 days, and then again at a 6-month follow-up visit. Steps taken will be collected daily until 42 days (the point where cross-over may occur) or discharge, whichever comes first. Follow-up data collection at 6 months will require an outpatient appointment or a home visit (Fig. 3). Data, including photographs of ulcers, will be collected on electronic tablets using the Research Electronic Data Capture (REDCap) system by local researchers.

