##### Activity measurement

We will also compare average daily step count between treatment and control groups as a simple difference in means (t test). Since one group may stay longer in hospital than the other and since there may be an interaction between rate of healing and step count, we will compare step counts over periods pre-set at 7, 14 and 42 days.

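### Step counts stop at discharge, which healing may trigger, so the 42-day t test can compare different stretches of stay and cannot support the claim that activity is excluded as a confounder

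*Protocol article*

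**What the plan says.** Under Intervention, Activity measurement, the pedometer is worn "from the first dressing change until 42 days (the point where cross-over may occur) or discharge, whichever comes first". Plans for assessment and collection of outcomes {18a} repeats this rule: "Steps taken will be collected daily until 42 days (the point where cross-over may occur) or discharge, whichever comes first".

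Discharge is tied to healing in two places. Outcomes {12} plans a check on early discharges "as complete healing may trigger discharge", and the Discussion says that "complete epithelialisation is a clinical decision that is also used to decide on discharge".

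The analysis is given in Methods for additional analyses {20b}, Activity measurement. The trial will "compare average daily step count between treatment and control groups as a simple difference in means (t test"). The same paragraph recognises that one arm may stay longer and that healing and steps may interact. Its answer is that "we will compare step counts over periods pre-set at 7, 14 and 42 days".

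The Discussion then draws the inference from these daily counts: "we can exclude activity as a confounding factor in any differences found in ulcer healing rates between intervention and control groups".

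**The concern.** Fixing the length of a window in advance does not fix the days that a person contributes to it. Recording still stops at discharge inside each window, so a person who heals on day 12 has a 42-day average made only of days 1 to 12. If one arm heals faster, its averages are weighted to early days and the other arm's averages include more late days. When activity drifts over the stay, or is related to healing speed, the two sets of averages differ for a reason unrelated to how active the arms were on any given day.

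Two further problems would remain without that distortion. A non-significant difference is not evidence of no difference. And steps are counted after an allocation that participants know (Who will be blinded {17a}), so an arm difference may result from treatment and is not a baseline imbalance.

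The stake is interpretive. Participants and practitioners are unblinded, and the protocol holds that activity is adversely associated with healing (Background and rationale {6a}). The step comparison is its stated check on differential rest. An artefact in one direction would invite readers to credit a real L-PRF effect to rest. A null result would be read as ruling out a difference that the data cannot rule out.

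**Working it through.** **Inputs from the protocol** (Sample size {14}): 70% v 90% healed by day 42, constant and proportional hazards, two-sided 5%, 80% power, 1:1, 65 recruited per arm.

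**Reproducing the protocol's own figure.** Hazards per day are −ln(0.3)/42 = 0.02867 and −ln(0.1)/42 = 0.05482, so the hazard ratio is 1.912. Schoenfeld's formula gives 4 × (1.960 + 0.842)² / (ln 1.912)² = 74.7, rounded up to 75 events. With a mean healing probability of 0.80, 75/0.80/2 = 46.9, which is the stated 47 per group.

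**Days contributed per person.** Assume discharge at healing (the protocol says only that healing may trigger it). Mean recorded days in a window of W days are (1 − e^(−λW))/λ, and the proportion still contributing at its end is e^(−λW).

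| Window | Mean days, control v L-PRF | Still contributing at end |
|---|---|---|
| 7 days | 6.3 v 5.8 | 82% v 68% |
| 14 days | 11.5 v 9.8 | 67% v 46% |
| 42 days | 24.4 v 16.4 | 30% v 10% |

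**Size of the artefact.** Suppose both arms have the same expected activity on every day, changing by b steps per day. A person observed for t days has an average shifted by about b × (t − 1)/2, so the arms differ by about b × (24.4 − 16.4)/2 = 4b in the 42-day window. For b = 30 that is about 120 steps/day; simulation in whole days gives about 118, with L-PRF lower.

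**False rejection by the t test.** The protocol gives no step mean, trend or SD. The following are assumed: 1000 steps/day at the start, 65 per arm, no arm effect on any day.

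| Rise per day | 42-day, SD 300 | 42-day, SD 800 |
|---|---|---|
| 0 | 5% | 5% |
| 15 | about 18% | about 7% |
| 30 | about 44% | about 12% |
| 45 | about 63% | about 20% |

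Over the same settings the 7- and 14-day windows stay at about 4–11%, with 7 days at about 5% throughout.

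**Sensitivity to healing times.** Keep 70% and 90% at day 42 but let healing cluster later (Weibull shapes 2 and 3, also assumed). Mean 42-day exposure becomes 29.8 v 23.7 and 32.7 v 27.9 days. For a rise of 30, rejection falls from 44% to about 31% and 23% at SD 300, and to about 9% and 7–8% at SD 800.

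**Precision of a null result.** With 65 per arm the 95% confidence interval half-width is 1.98 × √(2/65) = 0.35 SD. That is about 104 steps/day at SD 300 and 278 at SD 800, or 10% and 28% of a mean of 1000.

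**The case against.** The strongest reply is that the outcome is a per-day average, so unequal stay alone does not bias it. A bias needs activity to change over the stay or to be related to healing speed, and the protocol gives no trend. All participants are encouraged to rest, and a rise of 30 steps/day would take a person from 1000 to about 2,230 by day 42. This stands. It is why the rejection rates are conditional and run down to the nominal 5%. It does not remove the point, because the protocol itself expects that healing and step count may interact.

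Second, the protocol saw the problem and added short windows, and these are little affected. This also stands, and a reader who inferred that the authors overlooked unequal stay would be wrong. But the 42-day comparison is kept unchanged, and the short windows say nothing about days 15 to 42, while both primary endpoints run to day 42.

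Third, constant hazards place many healings early, and discharge may lag behind healing. Later clustering of healing narrows the gap in days and lowers the rates, as shown above, without removing either.

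Fourth, activity is not a primary outcome and enters neither primary model. This is correct. A reader might infer that the healing comparison itself is compromised; Statistical methods for main endpoints {20a} gives no ground for that, since the randomised intention-to-treat comparison does not use step counts. Nor do the documents support quoting a single high false-positive rate as the expected one, or the view that day 7 should replace day 42 as the lead comparison.

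**Conclusion.** The point holds for a supporting analysis and for the inference drawn from it. Recording that is cut off by discharge, together with a t test on person-averages, leaves the 42-day comparison open to an artefact whenever activity drifts over the stay or goes with healing speed. The gap of about 8 recorded days per person rests on the protocol's own healing assumptions plus discharge at healing. The size of the artefact depends on step values that the documents do not give, so it can be stated only as a range from none to substantial.

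The claim that activity can be excluded as a confounder fails whatever those values are. A non-significant t test leaves differences of roughly a third of an SD open, and a post-allocation measure cannot be treated as a baseline confounder. The distortion calculated here is a spurious difference; masking of a real one is possible in principle but was not quantified.

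**What to change.** 1. Keep the 7- and 14-day comparisons as planned.
2. For 42 days, replace the t test on person-averages with a day-matched analysis of the daily counts: a mixed model with day since first dressing change, arm and a participant random effect. It compares the arms at the same day of stay. It still assumes that, given the steps already recorded, discharge is unrelated to later activity, and this should be stated.
3. Report every between-arm difference in steps with a 95% confidence interval.
4. Reword the Discussion sentence to say that the size of any between-arm difference in activity will be reported, and that such a difference could be a consequence of allocation.

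The cost is analysis and wording only, because daily counts are already collected. No visits, participants or data items are added. The price is a weaker claim about activity than the Discussion now makes.

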### Trial status

Protocol version number: Version 2.0; 25.11.20

The TABLE trial is currently recruiting. The first patient was randomised on 18th September 2020. The Trial Management Group (TMG) and a Trial Steering Committee (TSC) met before the first patient was enrolled. We anticipate that it will take approximately 12–18 months to complete the recruitment phase.

## Abbreviations

AUC: Area under the curve
BSREC: University of Birmingham Biomedical and Scientific Research Ethics Committee
CONSORT: Consolidated Standards of Reporting Trials
DALY: Disability adjusted life year
ENL: Erythema Nodosum Leprosum
EQ-5D 3L: 5-Dimensional European Quality of Life Questionnaire
HIV: Human immunodeficiency viruses
HRQoL: Health-related quality of life
L-PRF: Leukocyte and platelet-rich fibrin
LMIC: Low- and middle-income countries
NHRC: Nepal Health Research Council
NIHR: National Institute for Health Research
NPIAP: National Pressure Injury Advisory Panel
PRP: Platelet-rich plasma
PUSH: Pressure Ulcer Scale for Healing
QALY: Quality adjusted life year
QoL: Quality of life
RCT: Randomised controlled trials
REDCap: Research Electronic Data Capture
RIGHT: Research and Innovation for Global Health Transformation (RIGHT)
TABLE: Trial of Autologous Blood products to promote ulcer healing in LEprosy
TMG: Trial Management Group
TSC: Trial Steering Committee
TB: Tuberculosis
TLMN: The Leprosy Mission Nepal
W-CAHRD: Warwick Centre for Applied Health Research & Delivery
WHO: World Health Organization
